### **6.11. Visit no.4 – Follow-up visit 29±6 months post-intervention**

29±6 months (35 months) after the end of the procedure, each participant will be seen for a long-term follow-up visit. This visit will include the same examinations as those performed in V1 and V3 except polysomnography and PET-Amyvid® examination.

The Cumulative Illness Rating Scale (CIRS) score will also be calculated, combining medical, biological, neuropsychological, and polysomnographic data collected at visits 1, 3, and 4.

Polysomnography is the reference method in this field, but it is extremely time-consuming and requires expertise both for the installation of electrodes and sensors and for the analysis of the tracings. During

the long-term follow-up of the participants, we will use a simpler and faster tool than polysomnography. The Dreem headband is a new EEG measurement tool that appears to be as accurate as polysomnography. It comes in the form of a headband with 5 dry electrodes (i.e. not requiring the application of a conductive paste) allowing the measurement of brain electrical activity, cardiac activity, respiratory rate and movements. It is easily placed on the participant's head, without any prior preparation. It takes less than three minutes to fit the headband to the participant's head and to move the hair away from the contact points of the electrodes. This headband will make it easier to collect sleep data, and will be proposed several consecutive nights at the participant's home in order to evaluate the impact of sleep variability, which is practically impossible with polysomnography.

In MRI2 session, the QSM sequence will not be performed because the signal-to-noise ratio does not allow to obtain usable scans. (Many QSM sequences in V1 and V3 are not valid.) It will be replaced by a 10-minute high-resolution DTI Locus sequence (HR-DTI-Locus), complementary to the HPC-T2 scan to understand the precise links between hippocampal substructures (HPC-T2), their connectivity and locus coeruleus substructures (HR-DTI-Locus) (Betts et al., 2019 Brain; Treit et al., 2018 Neuroimage).

[figure not shown]

Figure 8: Course of the MRI2 examination in V4 (the time spent in the MRI is indicated in orange with a total duration at the Cyceron center of approximately 120 min).

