### ***Polysomnography***

Two home sleep recordings will be performed for participants willing to perform this examination, using a portable device (Siesta, Compumedics, Australia). This examination consists of a continuous recording of an EEG, an electro-oculogram and an electromyogram performed on the chin muscles, and an electrocardiogram. EEG activity will be recorded at prefrontal, central, parietal, temporal and occipital leads according to the international 10-20 system, using Ag/AgCl electrodes with a ground at the vertex and a bi-mastoid reference. We will also record the ventilatory parameters in order to detect a possible sleep apnea syndrome and to quantify the apnea-hypopnea index. The realization of a polysomnography will allow the detection of a possible sleep apnea syndrome.

The interpretation of the respiratory recording collected during the polysomnography examinations is done by an expert, by visual scoring. The initial scoring of apneas and hypopneas was based on the criteria used in clinical practice and proposed by the Société de Pneumologie de Langue Française in 2010. However, the international criteria used in research in scientific publications are those of the American Academy of Sleep Medicine (AASM), revised in 2017. Consequently, we will calculate this scoring according to these new rules.

Given the already known cardiovascular risks and the potential impact on amyloid pathology and cognitive functions, it is important to be able to detect and treat this syndrome as early as possible in the older populations. Moreover, an effective treatment of this pathology is available (treatment by continuous positive pressure). In this respect, the trial brings a direct individual benefit to the participants.

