## **6.10. Visit no.3 – Follow-up visit**

At the end of the 18-month intervention, the participants will be welcomed back at the Cyceron center for a preliminary medical interview during which the physician will verify the absence of contraindication to the MRI examination (claustrophobia, ferromagnetic material in the body) and to the PET scan (known hypersensitivity to Amyvid® and Glucotep®), will update the participants' medical

history and drug treatments, and will declare any adverse events that may have occurred during this period. From the medical data collected during this interview, the comorbidity index will be calculated again (Charlson et al., 2008) as well as the CIRS score (see detailed description in V4). Then, the participants will be asked to perform again all the examinations of the inclusion visit (V1), namely:

- 2 MRI sessions,
- 2 PET Scans,
- a blood sample (3), conditioning the realization of the PET imaging to the same criteria as in V1 (cf 6.6),
- a detailed neuropsychological and behavioural assessment (V3),
- an examination of wakefulness (spontaneous EEG and MMN) and sleep.

Because some blood biomarkers and cognitive tests are not sensitive to longitudinal changes, they will not be repeated at this 18-month follow-up visit. Moreover, two behavioural tests (Cyberball (Williams et al., 2000) and Empathic Distractor (Klimecki et al., submitted); respectively evaluating social exclusion and empathy mechanisms), based on a surprise effect, can only be performed once and will be offered to non-expert seniors during this visit. A qualitative interview will be conducted with an evaluator experienced in conducting this type of interview (other than the neuropsychologists and members of the investigating team, this experimenter will be familiar with the intervention group). The open-ended semi-structured interview will last between 30 and 60 min and will be designed to collect data on the experience of learning English and meditation during their participation in the Age-Well trial. The V3 blood sample and the V3 neuropsychological and behavioural assessment are detailed in Tables 8 and 5 respectively.

The evaluators of the various examinations will not be aware of the participants' group assignment, and they will be instructed not to share it, except for the qualitative interview.

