### **Anthropometric data**

In order to improve the quality of anthropometric measurements (height, weight, BMI, abdominal girth and hip circumference), the acquisition of a body composition scale (Tanita MC-580) was made to allow accurate measurement of: Weight (kg), fat (%), body fat (kg), lean body mass (kg), hydration rate (kg), muscle mass (kg), bone mass (kg), impedance (Ohm), basal metabolic rate (kJ; kcal), visceral fat (level) and metabolic age (year), as well as BMI, Sarcopenic Index (SMI; kg/m^2) and Skeletal Muscle Mass (SMM; kg and %).

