**Sleep-related outcomes (OBJECTIVES 2, 4, 6, 7 and 9):**

- Subjective measures of sleep collected via sleep questionnaires
- Data collected by actimetrics record (mean duration of sleep, fragmentation indices during activity and resting states, regularity of the rest-activity cycle).
- Data collected during polysomnographic sleep record: Total sleep time, Sleep onset latency, Sleep efficiency, % of Stage N1, % of Stage N2, % of Stage N3, % of Stage REM sleep, Wake After Sleep Onset (WASO), Apnea-hypopnea index (/TST), Arousal index

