### **Objective 2bis (WP 1 to 6)**

The difference between the post-intervention measures (18 months) and the measures made 29 months after the end of the intervention for all cognitive, psychoaffective, life factors, sleep measures (and blood and imaging measures depending on budget availability) will be assessed within the 2 interventional groups. Analyses of the effect of the exposure to meditation/English learning (number of hours of practice, number of sessions...) will also be performed.

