**Objective 9 (WP 1 to 6)**

Comparison and correlations between measures at baseline, post-intervention (18 months) and 29 mois +/- 6 mois months after the end of the intervention in participants of the passive condition (control group) and participant' partners to identify the determinants of mental health and well-being in ageing, considering areas of cognition, psycho-affective/emotion, compassion, support, mindfulness, sleep, wellbeing and quality of life measures (and biological and radiological measures depending on budget availability).

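### Sleep EEG moves from polysomnography (V1, V3) to a headband at V4, so the planned within-group change from 18 months to V4 in EEG-derived sleep variables is either undefined or confounded with the device

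*Combined protocol and SAP*

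**What the plan says.** **V1.** Protocol section 6.6, Polysomnography: "Two home sleep recordings will be performed for participants willing to perform this examination, using a portable device". Electrodes are fitted at the training centre. The first night is for habituation, and the recording night follows about a week later. Section 10.6.2 has a sleep neurologist score the sleep EEG.

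**V3.** Section 6.10 has participants repeat the V1 examinations, including "an examination of wakefulness (spontaneous EEG and MMN) and sleep".

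**V4.** Section 6.11 schedules the "same examinations as those performed in V1 and V3 except polysomnography and PET-Amyvid® examination". In place of polysomnography, "we will use a simpler and faster tool than polysomnography": a headband with five dry electrodes, worn at home on several nights in a row. Tables 3 and 7 and section 10.2 agree that polysomnography is not done at V4.

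**Secondary SAP.**
- Objective 2bis assesses, within each of the two intervention groups, "The difference between the post-intervention measures (18 months) and the measures made 29 months after the end of the intervention". Sleep measures are included without exception.
- Objective 9 plans "Comparison and correlations between measures at baseline, post-intervention (18 months) and 29 mois +/- 6 mois months after the end of the intervention" in passive controls and in participants' partners, with sleep among the domains.
- Objective 2ter compares the 18-month-to-V4 change between the two intervention groups.
- The sleep outcomes list begins the EEG part with "Data collected during polysomnographic sleep record: Total sleep time, Sleep onset latency, Sleep efficiency". The headband does not appear.

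**The concern.** In a single-group comparison of 18 months with V4, every EEG-derived sleep variable (stages, latency, efficiency, total sleep time, wake after sleep onset) would come from one recording system at the first time point and another at the second. The number of nights and the habituation procedure change at the same moment. No adjustment within one group can separate these changes from elapsed time.

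Objective 2bis is meant to show whether intervention effects last. A systematic difference between headband and polysomnography could look like loss or gain of effect, or could hide a real loss. The same applies in Objective 9 to any comparison of sleep-EEG values across visits in the passive group.

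**Working it through.** **Is there any bridge between the two devices?** The protocol's only statement on comparability (section 6.11) is that the headband seems to match polysomnography in accuracy. It gives no figure or reference, and no visit has both recordings. By contrast, section 6.6 places the Somno-Art nights so that they include the second polysomnography night, in order to check agreement. Nothing similar is planned for the headband.

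**What would the SAP compute?** There are two readings.
1. Literal: the listed outcomes are polysomnographic. They have no V4 value, and the headband has no 18-month value, so no sleep-EEG change exists.
2. Substitution: the headband supplies the V4 value, as its role in section 6.11 suggests. The change is then time effect plus device effect.

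The substitution was not carried through elsewhere either. Sections 6.11 and 10.2 build the CIRS from a polysomnographic apnea-hypopnea index among data from visits 1, 3 and 4, although V4 has no polysomnography.

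**Illustration of the second reading.** The plan states no figure to reproduce.

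Inputs:
- Two-sided 5% per test (secondary SAP, Type I error rate).
- True change zero.
- Device offset δ, in SDs of the change score: an assumption, 0.1 to 0.5.
- n = 45: the Lockdown annex counts 135 seniors in April 2020, and 135 / 3 = 45 per arm.
- n = 50: the planned arm size (Table 1).
- n = 35: an assumed lower value.

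Formula: the paired t statistic follows a noncentral t distribution with n − 1 degrees of freedom and noncentrality δ√n. The rejection rate is the probability that |T| exceeds the 5% critical value. For n = 45, √45 = 6.71, so the noncentrality is 1.34 at δ = 0.2 and 2.01 at δ = 0.3. The second value is almost equal to the critical value of about 2.02, hence rejection close to one half.

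| δ | n = 35 | n = 45 | n = 50 |
|---|---|---|---|
| 0 | 5.0% | 5.0% | 5.0% |
| 0.1 | 8.9% | 10.1% | 10.7% |
| 0.2 | 21.0% | 25.9% | 28.4% |
| 0.3 | 40.7% | 50.3% | 54.8% |
| 0.5 | 82.0% | 90.7% | 93.4% |

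**Between-arm contrast.** If both arms carry the same offset, (Δ₁ + δ) − (Δ₂ + δ) = Δ₁ − Δ₂. A simulation of 20,000 runs with 45 per arm gave rejection of 5.0%, 4.8% and 5.1% at δ = 0.2, 0.3 and 0.5. Objective 2ter therefore keeps its level under a common offset.

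**The case against.** **The SAP never says that headband values will be subtracted from polysomnography values.** This stands. A reader might infer that a device difference will be reported as maintenance or loss of effect, but the documents do not go that far. They leave the V4 sleep-EEG variable unnamed. Section 6.11 also gives the headband a purpose of its own, night-to-night variability. The secondary SAP says that it is based on protocol v9.0 and v10.0, while the protocol is now v12.0, so the list may simply need updating. None of this removes the problem, because section 6.11 also presents the headband as the stand-in for polysomnography and Objective 2bis makes no exception for it.

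**Sleep stages may not be lost at V4.** This also stands. Section 6.11 excludes only polysomnography and PET-Amyvid, so Somno-Art appears to continue, and sections 10.1.2.5 and 10.6.2 say that it yields sleep stages, latency, efficiency and total sleep time. It would be wrong to conclude that no sleep-stage trajectory is possible, or that indirect calibration is ruled out, although none is planned.

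**The numbers of pairs are upper-end.** Polysomnography is for willing participants, and section 14.5 calls the long-term follow-up optional. At an assumed n of 25, rejection is about 16% and 30% at δ = 0.2 and 0.3. That is smaller, but still well above 5%.

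**The new body-composition scale.** Section 10.2 reports that "the acquisition of a body composition scale (Tanita MC-580) was made to allow accurate measurement", and a reader might see the same fault there. The documents do not support this. No 18-month body-composition value from an earlier instrument is described (sections 6.6 and 10.1.1.1 give weight, height and circumferences), and neither Objective 2bis nor Objective 9 in the secondary SAP names anthropometry.

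**Conclusion.** The point holds for EEG-derived sleep variables in within-group comparisons that span V4: Objective 2bis, and the visit-to-visit comparisons in passive controls under Objective 9. There the planned change is either undefined or inseparable from the switch in device, number of nights and habituation.

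The size cannot be taken from the documents. With an assumed offset of 0.2 to 0.3 SD of change and no true change, a nominal 5% test at n = 45 rejects about 26% to 50% of the time. The direction of any offset is unknown.

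The finding does not extend to questionnaires, actimetry or the primary outcomes, nor to Objective 2ter if the offset is equal across arms. Added measurement noise could still cost that comparison power. This concerns a subset of secondary outcomes and should be settled before the V4 sleep data are analysed.

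**What to change.** Amend the secondary SAP as follows.

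1. Name the headband variables as the V4 sleep-EEG outcomes, separate from the polysomnography outcomes at V1 and V3.
2. In Objectives 2bis and 9, do not compute within-group change from polysomnography to headband. Use only sleep measures collected with the same instrument at the visits compared: past-month PSQI, Insomnia Severity Index and Epworth (Table 6 schedules all three at V1, V3 and V4), actimetry and, if it is confirmed at V4, Somno-Art. Somno-Art is missing from the secondary SAP's sleep outcomes and would have to be added.
3. Analyse headband variables only as between-arm contrasts at V4, including each intervention against passive controls, with or without adjustment for the V3 polysomnography value. State the assumption that any device offset is common to the arms.

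The cost is SAP wording, with no new data collection. The loss is a polysomnography-grade within-group sleep-stage trajectory from 18 months to V4, which the design cannot estimate validly in any case. The CIRS definition should be reconciled with the absence of polysomnography at V4 in the same revision.

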#### **Neuropsychological and behavioural assessment on V4**

Each participant will be welcomed at the Cyceron center by their referent or an investigating psychologist to perform a set of cognitive tests. The battery of tests proposed will be identical to that proposed during the inclusion visit (see Table 5 above). A questionnaire on the practice of English or meditation following the intervention program will be proposed in order to evaluate the impact of the intervention in the long term on cognition, psycho-emotional factors, sleep and lifestyle. All the tests and questionnaires will be carried out during the post-intervention evaluation visit (V4) in 2 sessions of approximately 2 hours during which breaks will be scheduled .

**Calculation of the CIRS score (Cumulative Illness Rating Scale):** The CIRS provides an overall numerical measure of an individual's pathologies (Groot et al., 2003) and appears to be more subtle and

useful than the CCI (Charlson Comorbidity Index) for assessing the overall health status of participants. It is also more adapted to a population of older adults without serious pathologies. The CIRS will provide a more detailed assessment of the overall health status of the participants in the trial.

The CIRS score is calculated from medical (history, treatments), biological (Body Mass Index (BMI), Blood Pressure (BP), Blood Count (CBC), Exploration of Lipid Abnormality (EAL), Fasting Blood Glucose), neuropsychological (Mini-Mental State (MMS)), and the Apnea-hypopnea index (AHI) score from polysomnography, collected during visits 1, 3 and 4 collected in the eCRF.

### ***6.12. Significant health outcomes (information, follow-up, treatment)***

In case of detection of pathological abnormalities during the imaging or biological tests, the investigator will inform the participant and their regular physician. The results will be transmitted to the regular physician who will take charge of the participant's medical follow-up. These persons will benefit from a classical clinical follow-up by their regular physician(s).

### ***6.13. Termination of participation in the trial***

At the end of participation in the trial, participants will receive standard clinical follow-up by their regular physician.

### ***6.14. Premature termination of the trial***

In the event of premature discontinuation of the trial (withdrawal or withdrawal of consent), participants will receive standard clinical follow-up by their regular physician.

A participant is considered lost to follow-up when they stop the protocol follow-up without a reason known to the investigator, so that data collection cannot be conducted as planned. Participants lost to follow-up should be actively sought by the investigator.

A participant who wishes to withdraw their consent to participate in the research (as they is entitled to do at any time), is no longer followed within the framework of the protocol, but must receive the best possible care given their state of health and the state of knowledge at the time.

A withdrawal of consent is a decision, by an included participant to exercise their right to discontinue participation in a research study at any time during the course of follow-up, without incurring any prejudice as a result, and without having to provide a reason.

The investigator should identify the cause of the withdrawal of consent and assess whether it is possible to collect, for the participants included in the randomized clinical trial, the primary outcome variable at the time of withdrawal of consent.

Withdrawals of consent should be promptly notified to the sponsor. The reasons for and date of withdrawal of consent should be documented in the participant's case report and medical record.

No data will be collected after withdrawal of consent but previously collected data will be retained unless the participant objects in writing.

## **6.15. *Deviations from the protocol***

Deviations may concern all aspects of a research protocol: inclusion process, follow-up, measurement of judgment criteria, treatments. All deviations must be documented by the investigator and discussed at the Scientific Council.

Only dropouts lead to a termination of the follow-up. Even in the case of a deviation from the protocol, the participant's follow-up must be carried out until the end of the protocol.

### **6.15.1. Premature and permanent cessation of research treatment**

A participant is considered to be in treatment discontinuation when they stop treatment before the protocol date. Participants in early discontinuation continue to be followed as planned in the protocol. In no case should the planned follow-up be modified.

The participant who discontinues treatment must receive the best possible care given their state of health and the state of knowledge at the time.

### **6.15.2. Lost to follow-up participant**

A participant is considered lost to follow-up when they stop the protocol follow-up for no reason known to the investigator, so that data collection cannot be completed as planned.

Lost to follow-up participants should be actively sought by the investigator.

### **6.15.3. Incorrectly included participant**

A participant is considered to be wrongly included when they were actually included in the research even though they did not meet all the eligibility criteria. Participants who are wrongly included must be discussed by the Scientific Council. They must continue to be followed as per the protocol until a decision has been made by the Scientific Council.

## **6.16. Rules for the discontinuation of the trial**

### **6.16.1. Description of the rules for permanent or temporary cessation of part or all of the trial**

#### **Discontinuation of the trial by the investigator:**

In the event of an adverse event judged to be severe by the investigator and which could jeopardize the health of the participants, the coordinating investigator may stop the trial in agreement with the sponsor.

If a hypersensitivity or anaphylactic reaction occurs, the radiopharmaceutical administration should be discontinued immediately.

